**Table 1. Summary of outcome and process evaluation measurements**

| Outcome                                                 | Study Measurements                                                                                     | Timing                                               | Items |
|---------------------------------------------------------|--------------------------------------------------------------------------------------------------------|------------------------------------------------------|-------|
| Demographic factors                                     |                                                                                                        |                                                      |       |
| Parent/primary caregiver, child and family demographics | General demographics questions; PLH-YC in Thailand                                        | Baseline                                             | 23    |
|                                                         | Disability; Washington Group questions  (adapted)                                         | Baseline                                             | 2     |
| Child maltreatment                                      |                                                                                                        |                                                      |       |
| Child maltreatment: physical abuse and emotional abuse  | ISPCAN Child Abuse Screening Tool- Intervention – Physical and Emotional Abuse Subscales  | Baseline, the fourth and eighth weeks, and Post-test | 4     |
| Proximal outcomes                                       |                                                                                                        |                                                      |       |
| Positive parenting and positive parent involvement      | Alabama Parenting Questionnaire (APQ)                                                 | Baseline, the fourth and eighth weeks, and Post-test | 2     |
|                                                         |                                                                                                        | Baseline & Post-test                                 | 3     |
| Parenting stress                                        | Parental Stress Scale (PSS)                                                               | Baseline, the fourth and eighth weeks, and Post-test | 1     |
|                                                         |                                                                                                        | Baseline & Post-test                                 | 4     |
| Secondary outcomes                                      |                                                                                                        |                                                      |       |
| Attitudes to corporal punishment                        | Multiple Indicator Cluster Survey  : child discipline module                              | Baseline & Post-test                                 | 1     |

| Outcome                                              | Study Measurements                                                                                                      | Timing               | Items     |
|------------------------------------------------------|-------------------------------------------------------------------------------------------------------------------------|----------------------|-----------|
| Child behaviour problems                             | Child and Adolescent Behaviour Inventory (CABI) 
Three Problem Rating Scale                | Baseline & Post-test | 14
2   |
| Parental mental health                               | Depression Anxiety and Stress Scale 21 (DASS-21)  : depression subscale                                    | Baseline & Post-test | 7         |
| Parent exposure to IPV and intimate partner coercion | WHO Multi-Country Questionnaire on Women's Health and Domestic Violence against Women (WHO)                | Baseline & Post-test | 7         |
| Child/Adolescent exposure to risks                   | Adapted from those used in evaluations of ParentApp for Teens in Tanzania and ParentText in South Africa                | Baseline & Post-test | 7         |
| Online safety                                        | Global Kids Online - Hurtful and bullying behaviour subscale                                               | Baseline & Post-test | 2         |
| Child learning and development                       | Multiple Indicator Cluster Survey (MICS)  : early childhood development                                    | Baseline & Post-test | 6         |
| Parent support of education                          | Adapted from those developed for Rosie Ceballo's Latino Family                                             | Baseline & Post-test | 5         |
| Process evaluation outcomes                   |                                                                                                                         |                      |           |
| Implementation fidelity                              | Facilitator checklists                                                                                                  | Post-test            | n/a       |
| Programme adherence                                  | Attendance registration                                                                                                 | Post-test            | n/a       |
| Participant satisfaction                             | Parent/primary caregiver overall satisfaction questionnaire subscale of those used in evaluations of PLH-YC in Thailand | Post-test            | 5         |
| Facilitator and participant engagement               | Process monitoring reports                                                                                              | Post-test            | n/a       |
| Acceptability and feasibility                        | Qualitative interviews                                                                                                  | Post-test            | n/a       |
| Total items at baseline                       |                                                                                                                         |                      | 90 |
| Total items at the fourth and eighth weeks    |                                                                                                                         |                      | 7  |
| Total items at post-test                      |                                                                                                                         |                      | 70 |

## C.4 Outcome data analysis

Stata 17 will be used for the analysis of general demographic data and the effectiveness of the programme as follows:

Descriptive statistics will be employed to analyse the general demographic data. The average and standard deviation will be used for the continuous data unless that data obviously violates a normal distribution. If the data is obviously a non-normal distribution, the median and interquartile ranges will be used. In addition, frequency and percentage values will be utilised for the categorical data.

All intervention effects will be evaluated utilising an intention-to-treat design, that includes all participants recruited in the study regardless of whether they complete the programme or all the assessment points . To handle missing data, the imputation or deletion method might not be suitable due to the limited sample size. We plan to manage this problem as follows:

- 1) For general demographic information, there is only a measurement time point. Once the data is collected by facilitators before programme delivery, the data will be checked immediately for completion. If any part of the information is found to be incomplete, we will try our best to contact the participants through various channels to request as much information as possible during the period that the participants remain in the programme.
- 2) The missing data in the primary or secondary outcomes will be carried out in the same way as the general demographic. The data will be checked immediately at each time point of the data collection. If any part of the information is found missing, it needs to be followed up on during the time that the participants are still in the project. In the event that the missing data occurs because participants drop out, we will try to contact the participants to find out whether their dropout is related to any factors in the project. If it is evident that there are conflicts or other project-related reasons leading to dropouts, the issues will be addressed to resolve them. If the dropout occurs randomly or it is just a personal reason, the project will go on, and the data will be followed up as much as possible. However, if there are data from at least two time points in each outcome, it is adequate for longitudinal data analysis using multilevel methods, and the missing data does not need to be imputation.

To evaluate the hypothesis regarding measuring effectiveness on primary and secondary outcomes, two-tailed tests given a type I error of  $p(\alpha) < 0.05$  and power = 0.8 will be used. Along with the estimated values, 95% confidence intervals and p-values will be presented. Multilevel analysis (MLA) was used to analyse the results because the data is multilevel structured. The data from repeated measurements taken at different times makes up the lowest level. The second level is the individual level, and the third level is the level of sub-district. Primary and secondary outcomes that are on a frequency scale, including child maltreatment, positive parenting, parent exposure to IPV, child/adolescent exposure to risks, online safety, and child learning and development, which are discrete data, will be utilise distribution testes to determine whether to use a Poisson regression or a negative binomial regression if the data is overdispersion. For the ordinal scale outcomes, including parenting stress, attitudes toward corporal punishment, child behaviour problems, parental mental health, and parent support for education, we will use a linear regression to measure the differences between the two groups. A two-level model will be performed comparing post-intervention effects across all outcomes, controlling for baseline and the random effect will be the cluster, and participants ID. In addition, a three-level model will be performed comparing time trends across child maltreatment and proximal outcomes.

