### *Allocation*

The 12 sub-districts will be randomly assigned using a 1:1 allocation ratio to either the intervention or control group using a computer programme after baseline assessment, and the groups will be set up. The random sequence will be produced by an outside researcher working at the HIV Netherlands Australia Thailand Research Collaboration (HIV-NAT) who is not directly participating in the project. Following the gathering of baseline data, the project coordinator and co-investigator will contact participants via telephone to inform them of their allocation status, ensuring that participants are blinded to their status throughout the initial evaluation.

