### Primary outcome

#### *1. Child maltreatment – physical abuse and emotional abuse*

Four items adapted from a reduced version of the International Society for the Prevention of Child Abuse and Neglect (ISPCAN) Child Abuse Screening Tool-Trial Parent version (ICAST-TP)  will be used to determine physical abuse and emotional abuse. The evaluation will be repeated four times consisting of the evaluation at baseline, post-test, and every four weeks during programme delivery. This study will evaluate the incidence of child abuse both in overall abuse by combining all subscales of two items assessing physical abuse and two items assessing emotional abuse. Participants report on the incidence of violent discipline use over the past four weeks using a frequency score of 0 to 8 or more times (e.g., how often did you discipline by spanking, slapping, or hitting with their hand over the past 4 weeks.).

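### The rule for recovering missing outcome answers has no cut-off at allocation, so baseline abuse items may be answered after parents know their arm

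*Protocol*

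**What the plan says.** Section C.4 (Outcome data analysis) has two numbered items on missing data. Item 1 covers demographics, which are measured once, before programme delivery. For gaps, staff are to contact the parent and "request as much information as possible during the period that the participants remain in the programme". Item 2 carries this over to the outcomes: "The missing data in the primary or secondary outcomes will be carried out in the same way as the general demographic". It adds a prompt check, "The data will be checked immediately at each time point of the data collection", and then, for any gap, "it needs to be followed up on during the time that the participants are still in the project". It gives no closing date, does not mention allocation, and does not say which period a late answer should describe.

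Three other places bear on this:

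- C.1, Allocation: sub-districts are randomised after baseline and parents are then told by telephone, "ensuring that participants are blinded to their status throughout the initial evaluation".
- C.3: the primary outcome has a moving window, "Participants report on the incidence of violent discipline use over the past four weeks". Positive parenting, child behaviour and depression look back two weeks, partner violence one week, and exposure to risks one month.
- C.4, later: the post-test model is described as "comparing post-intervention effects across all outcomes, controlling for baseline". A three-level model compares time trends for abuse and the proximal outcomes.

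**The concern.** A rule that is harmless for education or marital status is not harmless for a question about the past four weeks. When such a question is answered depends on when the gap is filled, and that decides both the period described and what the parent knows.

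Gaps in these items are plausible. C.2 treats the abuse and partner-violence sections as sensitive, and D.2 tells parents that they need not answer questions that make them uncomfortable.

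Two things are at stake. First, a covariate meant to precede randomisation could be collected after disclosure, in one arm from parents already receiving the programme. Adjusting for it can remove part of the effect or add to it. Second, a week-4 gap filled near week 8 blurs the separate week-4 and week-8 effects that objective 1 in B.3 asks for.

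**Working it through.** **Does the rule reach baseline data after allocation?** Demographics exist only at baseline, yet item 1 lets them be completed while the parent is in the programme. The programme starts after allocation (C.1) and runs for nine weekly sessions. Item 2 applies the same treatment to outcomes. So the text permits a baseline outcome item to be answered after disclosure. If the four-week abuse question is asked as worded in programme week 5, its recall period lies inside the programme.

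**The plan's own figures.** Inputs from C.1, Sample size: IRR 0.57 used as a hazard ratio, two-sided 0.05 (two-tailed per C.4), power 0.80, 1:1. With hazards 1 and 0.57 (mean 0.785):

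N = [1.960 × √(4 × 0.785²) + 0.842 × √(2 × 1² + 2 × 0.57²)]² / 0.43² = 106.96, so 54 per arm and 108 in total.

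Then 108 / 0.9 = 120, and 120 × 2 = 240. All three stated figures reproduce, and this point does not change them.

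**Size for a change-from-baseline contrast.** Let f be the share of baseline scores taken late (assumed) and r the rate ratio in force in the intervention arm at that moment (assumed). Late control answers are unaffected on average. The estimated ratio becomes

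0.57 / (1 − f(1 − r)).

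| f | r = 0.57 | r = 0.75 | r = 1 |
|---|---|---|---|
| 5% | 0.583 | 0.577 | 0.570 |
| 10% | 0.596 | 0.585 | 0.570 |
| 20% | 0.624 | 0.600 | 0.570 |

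**Size for the baseline-adjusted model.** This is closest to the post-test model in C.4. It was simulated as a negative binomial regression on log(1 + baseline), in two ways.

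- Large samples without clustering (mean count 4, log-normal between-parent SD 1, latent baseline-to-post correlation 0.7, total capped at 4 × 8 = 32).
- Trials of 12 clusters × 18 = 216 parents with four items each capped at 8. Two scenarios were run; the first is shown.

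| Setting | none late | 5% | 10% | 20% |
|---|---|---|---|---|
| Large sample, r = 0.57 | 0.577 | 0.582 | 0.591 | 0.601 |
| Large sample, r = 0.75 | 0.573 | 0.580 | 0.580 | 0.591 |
| Large sample, r = 1 | 0.575 | 0.575 | 0.576 | 0.577 |
| Large sample, r = 1.25 | 0.575 | 0.572 | 0.565 | 0.563 |
| 216 parents, whole score late, r = 0.57 | 0.601 | 0.612 | 0.619 | 0.636 |
| 216 parents, two of four items late, r = 0.57 | 0.601 | 0.607 | 0.611 | 0.621 |

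The starting values differ slightly between rows through simulation noise. They lie above 0.57 mainly because of the caps. Where r is below 1, the shift at 10% to 20% late runs from 0.580 − 0.573 = 0.007 to 0.636 − 0.601 = 0.035.

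**Against the trial's precision.** Eighty per cent power at IRR 0.57 implies a standard error of log-IRR of 0.562 / 2.802 = 0.20. In the first row, the 10% and 20% shifts are ln(0.591/0.577) = 0.024 and ln(0.601/0.577) = 0.041, or about 0.1 and 0.2 standard errors.

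**The case against.** The best defence is that late filling should be rare. C.4 requires an immediate check. In C.2 the data collector sits with the parent and enters answers on a tablet. C.5 adds review by a lead collector, daily transmission and timely correction. Allocation follows baseline, so the natural order is check, complete, then allocate. Completion windows may also sit in the data-collection manual, and a late call could ask about the original dates.

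Most of this stands as an argument about frequency. It does not close the gap, because a check is not a deadline and item 1 expressly carries baseline-only data into the programme period. Nor can an analysis plan repair it afterwards: it cannot restore a pre-allocation answer, and it can set late ones aside only if they are dated. Asking about the original dates would correct the recall period but not the parent's knowledge of her arm.

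Two stronger readings are tempting and not supported.

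- A reader might infer that C.4 contradicts the Allocation section. It does not direct that baseline be collected after disclosure; it permits it, and so leaves the intended blinding unprotected.
- A reader might infer that the bias always runs towards no effect. With r = 1 it is nil. With r = 1.25 the adjusted ratio falls from 0.575 to 0.563 at 20% late. Parents who know their arm and are learning to notice harsh discipline could report more of it.

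**Conclusion.** The point holds as a defect in a stated collection rule. Moving-window outcomes are put under a recovery rule made for fixed facts, with no cut-off at allocation or programme start. A pre-randomisation covariate should not be obtainable after disclosure, whichever way the bias runs.

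The likely harm is small. At assumed late shares of 10% to 20%, with the programme already lowering reported abuse, the baseline-adjusted IRR moves by about 0.01 to 0.04 towards 1. The larger series (0.583 to 0.624) belongs to a change-from-baseline contrast and should not be read as the shift in the covariate-adjusted model. The late share, the early rate ratio and the count-model settings are all assumptions; the protocol gives none of them. The change is worth making because it is cheap and cannot be made after the data are in.

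**What to change.** Split item 2 of the missing-data text in C.4 from item 1:

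- Keep open-ended recovery for fixed demographics only.
- Complete baseline outcome items only before the sub-district's allocation is disclosed.
- For week 4, week 8 and post-test, allow completion only within a short fixed number of days, asked about the original recall dates by the blinded data collector.
- Date every recovered answer, and treat anything later as missing for that time point.
- Reconcile the recall periods so that the original window is defined: C.2 describes the assessments during delivery as covering two weeks, while C.3 gives four weeks for abuse.

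The cost is a few sentences in the protocol and the collectors' manual, and a few more missing items. A parent without a complete baseline score could fall out of the baseline-adjusted model, so the text should say how such parents are kept. For abuse and the proximal outcomes, the longitudinal multilevel model already planned can do this. The secondary outcomes are measured only twice, so a parent lacking baseline has a single time point there, and the plan needs a sentence on that case. The sample size is unaffected.

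### The two-level post-test model has a mis-specified participant random effect and leaves out anyone without a post-test, so it does not deliver the stated intention-to-treat analysis

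*Protocol*

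**What the plan says.** All of this is in Protocol section C.4 (Outcome data analysis) unless noted.

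- **Population.** The intention-to-treat analysis "includes all participants recruited in the study regardless of whether they complete the programme or all the assessment points".
- **Missing data.** The protocol says that "the imputation or deletion method might not be suitable due to the limited sample size". It then relies on follow-up efforts and on this rule: "if there are data from at least two time points in each outcome, it is adequate for longitudinal data analysis using multilevel methods", without imputation.
- **Hierarchy.** Repeated measurements are the lowest level. "The second level is the individual level, and the third level is the level of sub-district".
- **Post-test model.** "A two-level model will be performed comparing post-intervention effects across all outcomes", with these terms: "controlling for baseline and the random effect will be the cluster, and participants ID".
- **Longitudinal model.** In addition, "a three-level model will be performed comparing time trends across child maltreatment and proximal outcomes".
- **Distributions.** Frequency outcomes, including child maltreatment, are tested "to determine whether to use a Poisson regression or a negative binomial regression if the data is overdispersion". Parenting stress, attitudes to corporal punishment, child behaviour, parental mental health and support of education are analysed by linear regression.

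Table 1 (section C.3) schedules child maltreatment at four occasions and all eight secondary outcomes at baseline and post-test only.

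**The concern.** There are two faults, and they meet in the same sentence.

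First, the random effects do not fit the data that the model uses. A model of the post-test score adjusted for baseline has one record per participant, so participant is already the residual level. A separate participant effect adds nothing in a linear model and changes meaning in a count model. A model that really had repeated rows within participants within sub-districts would have three levels by the protocol's own hierarchy, not two.

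Second, the same model cannot include a participant with no post-test, yet the population statement says that such participants are included. For the secondary outcomes no other model is planned. A reader of the trial report would be told that everyone recruited was analysed when only those with an observed post-test were. The missing-data assumption behind the estimate would go unstated.

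**Working it through.** **1. The plan's own sample size.** Inputs from section C.1 (Sample size): rate ratio 0.57 used as a hazard ratio, power 0.80, 1:1 allocation, attrition 10%, design effect 2. Section C.4 gives two-sided testing at 0.05. For the exponential comparison of two hazards without censoring, take h1 = 1, h2 = 0.57, and mean 0.785:

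N = [1.960 × √(4 × 0.785²) + 0.8416 × √(2 × 1² + 2 × 0.57²)]² / (1 − 0.57)² = 106.96, or 108 in equal groups.

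108 / 0.90 = 120, and 120 × 2 = 240. The protocol's figures reproduce.

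**2. Who has a row in the post-test model.** 240 × (1 − 0.10) = 216 analysed, 24 left out. This takes the planning attrition as the rate of missing post-tests. At other assumed rates:

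| Missing post-test | Left out of 240 | Power, protocol's method, design effect 2 |
|---|---|---|
| 5% | 12 | 0.824 |
| 10% | 24 | 0.804 |
| 15% | 36 | 0.782 |
| 20% | 48 | 0.757 |
| 30% | 72 | 0.702 |

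At 10% the effective size is 216 / 2 = 108, the planned minimum, so power holds.

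**3. Whether the two-time-point rule keeps them.** For a secondary outcome, a missing post-test leaves one time point (baseline). The rule needs two, so it keeps none. For child maltreatment, baseline plus week 4 or week 8 satisfies the rule, and the three-level model can use those data. The full positive parenting and parenting stress scales resemble the secondary outcomes: only two of five and one of five items, respectively, are asked at weeks 4 and 8.

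**4. Whether the participant variance can be estimated with one row each.**

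- *Linear.* The covariance is σ²(cluster) within sub-district plus [σ²(participant) + σ²(residual)] on the diagonal, so only the bracketed sum enters the likelihood. On simulated data of the trial's shape (12 clusters of 20), the log-likelihood was −109.51056872 with the participant share of that sum set at 0, 0.25, 0.50, 0.75 and 0.99. The split is not identifiable.
- *Poisson.* The variance is tied to the mean, so extra variation is visible. On 240 simulated counts with an assumed participant standard deviation of 1 and no cluster effect, the profile log-likelihood was −804.5 at 0.01, −593.1 at 0.5, −558.6 at 1.0 and −605.7 at 2.0. There is a clear maximum, so the effect is estimable as overdispersion.
- *Negative binomial.* The dispersion parameter already represents variation between single records, so a participant effect largely duplicates it. This is by reasoning; it was not computed.

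**5. The alternative reading.** If controlling for baseline meant entering baseline as a repeated response, baseline-only participants would stay in and a participant effect would be estimable. The model would then have occasion, participant and sub-district levels, and could not be called two-level. Neither reading makes the sentence consistent.

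**The case against.** The strongest case is that little is lost in practice.

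- *Week 4 and week 8 data are not wasted.* A reader might infer that the whole analysis is complete-case. The documents do not support that, because the three-level model uses the interim abuse data. Precedence between models is also often settled in a statistical analysis plan, which is not at hand. What stands is that the protocol itself fixes the post-test model for every outcome and presents the other as an addition for time trends.
- *The participant effect is not always inestimable.* This is correct: non-identifiability is confined to the linear models. There the treatment estimate is unaffected by the variance split, so the cost is an ill-defined model or a convergence problem, not bias.
- *Deletion is not rejected.* This is also correct. The protocol only says that it may be unsuitable, so the conflict is with the population statement, not with a ban on deletion.
- *Loss may not differ by arm.* One might argue that only the intervention arm has a programme to leave. But leaving the programme is not missing an assessment: the protocol plans follow-up of dropouts and a telephone fallback. Nothing in it shows post-test loss differing by arm.
- *Baseline-only participants add almost nothing.* For outcomes measured twice, a baseline-adjusted analysis of observed post-tests is already valid if missingness depends on arm and baseline. Forcing those participants into a two-time-point mixed model, or imputing them, would rest on essentially the same assumption and is a matter of preference. For these outcomes the fault is therefore in the stated population.

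**Conclusion.** The point holds in this limited form. The post-test model claims a property it does not have and carries a random-effects structure that contradicts the protocol's own hierarchy.

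The participant effect is unidentifiable for the five linear outcomes. It is only an overdispersion term under Poisson, and largely redundant under negative binomial. At the planned attrition, 24 of 240 recruited participants fall outside the model, and the missing-data rule recovers none of them for the eight secondary outcomes. For child maltreatment the remedy is already planned but has no stated precedence.

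This rests on reading post-test as the response with baseline as covariate, and on 10% as the rate of missing post-tests. It does not show a loss of power at that rate, nor a biased treatment effect.

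**What to change.** 1. In any linear or negative binomial model with one row per participant, remove the participant random effect and keep sub-district as the random effect. If a Poisson model keeps a participant term, describe it as overdispersion.
2. For child maltreatment, make the already planned three-level longitudinal model primary, with categorical time and arm-by-time terms. Report the arm contrast at one month post-intervention as the result, and keep the post-test model as a sensitivity analysis.
3. For the secondary outcomes, replace the claim to analyse all recruited participants. State that those with an observed post-test are analysed, assuming data are missing at random given arm and baseline.

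The cost is protocol wording and analysis code; no extra participants or visits are needed. Two matters must be settled before step 2 can work:

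- **Recall window.** Section C.2 says the interim assessments cover the past two weeks, while section C.3 gives four weeks for the abuse items. These must be reconciled, or the four occasions are not on one scale.
- **Who is surveyed.** The protocol summary (Data collection and analysis) assigns the week 4 and week 8 surveys to programme participants, whereas the first objective implies a comparison of arms. The protocol should confirm that both arms complete them.
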